### Patient population

Participants will be identified from patients attending the rapid access chest pain clinic. We will recruit 4,138 patients, randomized 1:1 to standard care (*n* = 2,069) or standard care with coronary calcium score and CT coronary angiography (*n* = 2,069).

Inclusion criteria will be: (i) attendance at the rapid access chest pain clinic and (ii) age over 18 years but less than or equal to 75 years.

Exclusion criteria will be: (i) inability or unwillingness to undergo CT scanning; (ii) exceeding the weight tolerance of scanner; (iii) known severe renal failure (serum creatinine >200 μmol/l or estimated glomerular filtration rate <30 ml/min); (iv) previous recruitment to the trial; (v) major allergy to iodinated contrast agent; (vi) inability to give informed consent; (vii) known pregnancy; or (viii) acute coronary syndrome within 3 months.

### Participant selection and enrolment

The trial is a pragmatic evaluation of the added value of CT coronary angiography in a rapid access chest pain clinic. Only patients attending the rapid access chest pain clinic will be approached to participate. The inclusion and exclusion criteria are broad and inclusive, and should enable rapid identification of eligible patients attending the clinic.

Patients will be given a patient information sheet on arrival at the rapid access chest pain clinic. After consultation, all eligible patients will be approached to enter the trial by the attending clinician. Written informed consent will be obtained from patients willing to participate in the study (Figure 1).

**Figure 1 F1:**
[figure not shown]
**Rapid access chest pain clinic attendance, eligibility and recruitment.** (CHD, coronary heart disease; CT, computed tomography; ECG, electrocardiogram; HDL, high dependency lipoprotein).

### Randomization

Following recruitment, patients who agree to undergo research evaluation will be randomized (1:1), either to no additional scanning or to undergo further evaluation with coronary calcium scoring and CT coronary angiography within 14 days of clinic attendance and before invasive coronary angiography or other cardiac investigations. Randomization will be conducted using a web-based system to ensure allocation concealment and will incorporate minimization to ensure matching for age, sex, body mass index (height and weight), diabetes mellitus, prior history of coronary heart disease, atrial fibrillation and baseline diagnosis of angina due to coronary heart disease.

### Equipoise

Attending clinicians in the rapid access chest pain clinic will not be permitted to investigate patients with CT coronary angiography unless the patient is randomized to receive the scan as part of the trial. During the course of the trial, it is anticipated that CT coronary angiography may start to be introduced into routine clinical practice within the rapid access chest pain clinic setting. It will be important that loss of equipoise does not prejudice the trial. This practice will, therefore, be discouraged during the course of the trial. Where this is not feasible, either the trial centre will be closed or all patients will be approached to participate in the trial but, where a patient is randomized to standard of care, they will be excluded from undergoing a CT coronary angiogram and an alternative noninvasive test will be selected. Equipoise will be monitored through data collected on unrecruited patients.

### Study assessments and data collection

#### Clinic assessment

All patients will undergo routine evaluation at the rapid access chest pain clinic including, where appropriate, symptom-limited exercise electrocardiography using the standard Bruce protocol. Patients will be categorized as low, intermediate or high risk by the attendant clinician, informed by the NICE guideline [20]. In general, high-risk patients will be treated for coronary heart disease and undergo invasive coronary angiography (10%), and low-risk patients (10%) will be reassured and discharged. Intermediate-risk patients (80%) will be treated and further investigated at the discretion of the clinician. In all cases, the diagnosis and agreed management strategy will be documented at the end of the clinic attendance. Cardiovascular risk will be calculated using previously established risk scores, such as the ASSIGN and Framingham scores.

The study data sheet will be used in the rapid access chest pain clinic to document patient history, examination and management plan for all patients (recruited and unrecruited). This will be completed by the attending clinician or nurse. This will also include assessment of eligibility. The study pro forma for all ineligible participants and eligible unrecruited participants will be retained in an anonymized form to provide detailed data on these patients in comparison with the study participant population. All study pro formas (recruited and unrecruited eligible and ineligible patients) and consent forms (recruited participants) will be collated by the trial manager and entered into the database.

#### Blood tests

If the participant has not had total cholesterol and HDL (high-density lipoprotein) cholesterol levels measured within the past three months, a blood test will be taken at the rapid access chest pain clinic. If the total cholesterol is above 7.0 mmol/l or the HDL is below 0.5 mmol/l, the primary care physician will be informed by letter, as this may warrant treatment irrespective of the patient’s 10-year cardiovascular risk.

In a sub-group of patients, a venous blood sample will be obtained and stored for future assessment of biomarkers.

#### Computed tomography

Computed tomography scans will be performed using a 64, 128 or 320-multidetector scanner. Computed tomography protocol optimizations will be performed at all sites throughout the study, to optimize scanning parameters, such as radiation dose and contrast administration.

##### Medication

Before calcium scoring, patients with a heart rate of greater than 60 beats/min and systolic blood pressure >110 mmHg will receive rate-limiting medication. If a participant’s heart rate is above 100 beats per minute despite rate-limiting medication, CT coronary angiography will not be performed. A small dose of oral diazepam may be prescribed for anxious patients, to improve heart rate control. Sublingual glyceryl trinitrate will be administered immediately prior to CT imaging.

##### Coronary artery calcium score

Coronary calcium scoring will be performed prior to coronary angiography. Investigators blind to patient characteristics will conduct off-line analyses using automated computerized software programs that employ the Agatston scoring method [21] using a threshold of 130 Hounsfield units [11]. The calcium score percentile based on age and sex will be calculated using coronary artery calcium score distributions from the Multi-Ethnic Study of Atherosclerosis (MESA) [22]. This will be performed using a web-based calculator, available at http://www.mesa-nhlbi.org/Calcium/input.aspx. For patients younger than 45, 45 years will be used for the calculation of the calcium score percentile.

##### Computed tomography coronary angiography

Coronary angiography will be conducted during contrast enhancement using pre-specified protocols (as recommended by the scanner manufacturers) during a single breath hold with prospective electrocardiographic gating as appropriate.

### Image assessment

All CT and invasive coronary angiograms will be assessed by at least two trained observers. Angiograms (CT and invasive) will be reviewed independently and without prior knowledge of the alternate angiogram. Where there is disagreement between paired observers (but not modalities), angiograms will be reviewed and classified by consensus. Angiograms will be reported using the 15-segment model [23]. Significant stenosis due to coronary artery disease will be defined as a stenosis greater than 70% in one or more major epicardial vessels or greater than 50% in the left main stem [20]. Luminal cross-sectional area stenoses will be classified as normal (<10%), haemodynamically insignificant (10-49%), intermediate (50-70%), significant (greater than or equal to 70%) or total or subtotal occlusion (100%).

### Definition of coronary artery disease

Coronary artery disease will be classified as: (a) obstructive coronary artery disease, atherosclerotic plaque encompassing a luminal cross-sectional area of ≥70% in at least one major epicardial vessel; (b) nonobstructive coronary artery disease, either atherosclerotic plaque encompassing a luminal cross-sectional area of <70% but >10% in at least one major epicardial vessel, or a calcium score >400 AU (Agatston units) or >90th percentile for age and sex; or (c) minimal or no coronary artery disease. Significant plaque burden is defined as atherosclerotic plaque causing >10% luminal cross-sectional area stenosis.

### Management recommendations

Computed tomography scans will be reported locally by two trained observers (radiologist and cardiologist). The CT report will also include recommendations for management, including primary or secondary prevention. Treatment of angina due to coronary heart disease will be at the discretion of the responsible consultant. (Figures 2 and 3). For participants in the no-CT-scan group, the responsible consultant will be sent a letter detailing the patient’s ASSIGN score.

**Figure 2 F2:**
[figure not shown]
**Computed tomography coronary angiography results and diagnosis documentation.** (CHD, coronary heart disease; CT, computed tomography).

**Figure 3 F3:**
[figure not shown]
Plan of investigation (CHD, coronary heart disease; CT, computed tomography; CVD, cardiovascular disease).

### Symptom outcomes

At baseline, 6 weeks and 6 months, chest pain will be assessed by the UK version of the Seattle Angina Questionnaire (SAQ-UK) [24] and quality of life will be assessed by the 12-Item Short Form Health Survey (SF-12®). The standard (4-week) recall second version of the SF-12® will be used (SF-12v2™). The SF-12 Physical Component Summary (PCS) and Mental Component Summary (MCS) scores will be calculated, along with utility scores based on the SF-6D algorithm.

Baseline questionnaires will be handed to the patient at the end of the rapid access chest pain clinic consultation. At 6 weeks and 6 months, questionnaires will be posted to participants, with telephone follow-up for nonresponders after two mailings two weeks apart.

### Diagnostic outcomes

The proportion of patients diagnosed with coronary heart disease will be documented at baseline, after CT (where appropriate), after 6 weeks and after 6 months. This will be defined as (i) prior history of coronary heart disease (previous documented acute myocardial infarction (universal definition), obstructive coronary heart disease (≥70% luminal stenosis in at least one major epicardial vessel on invasive coronary angiography) or previous coronary revascularization (percutaneous coronary intervention or coronary artery bypass surgery)), (ii) clinical diagnosis of angina pectoris due to coronary heart disease, or (iii) obstructive or nonobstructive CT diagnosis of coronary heart disease. The extent of coronary heart disease will be determined by the number of vessels affected (none, one, two or three vessels diseased (≥70% luminal stenosis of a major epicardial vessel)) and plaque load determined by CT coronary angiography.

The accuracy of the CT coronary angiography will be determined by comparison with invasive coronary angiography (gold-standard) for the assessment of the number of vessels affected. The extent of plaque burden cannot be compared between the two modalities.

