### Secondary endpoints

The following secondary endpoints will be evaluated: (i) the frequency and severity of chest pain symptoms at six weeks and six months; (ii) the CT observed presence and extent of coronary artery disease; (iii) the diagnosis and severity of coronary heart disease; (iv) the accuracy of CT coronary angiography compared with the gold-standard of invasive coronary angiography in those who receive both investigations; (v) the effect on investigations, unscheduled care and healthcare resource utilization; and (vi) the effect on patient management, including secondary prevention, anti-anginal therapy (pharmacological therapy and coronary revascularization), and treatment of noncardiac chest pain (such as hiatus hernia).

The study has been primarily set up to assess a patient-focused symptom outcome. However, alterations in management may result in long-term benefits to patients. Therefore long-term outcomes will be assessed, including: (i) cardiovascular death or nonfatal myocardial infarction; (ii) cardiovascular death; (iii) nonfatal myocardial infarction (universal definition); (iv) cardiovascular death, nonfatal myocardial infarction or nonfatal stroke; (v) nonfatal stroke; (vi) all causes of death; (vii) coronary revascularization, percutaneous coronary intervention or coronary artery bypass graft surgery; (viii) hospitalization for chest pain, including acute coronary syndromes and noncoronary chest pain; and (ix) hospitalization for cardiovascular disease, including coronary artery disease, cerebrovascular disease and peripheral arterial disease.

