### Investigation outcomes

Relevant investigations will be documented for each participant at the baseline clinic attendance, after 6 weeks and after 6 months. This will include: an exercise electrocardiographic stress test; nuclear medicine imaging - myocardial perfusion imaging; stress echocardiography; invasive coronary angiography; and noncardiac investigations, for example, endoscopy.

This will be documented by the clinician in charge of patient care in response to the CT coronary angiogram report. Further information will be obtained from electronic hospital records and patient surveys. Computed tomography coronary angiography will be performed prior to any invasive coronary angiogram, to facilitate a decision to undertake or cancel this invasive investigation.

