## Discussion

The multicentre randomized controlled SCOT-HEART trial will assess the added value of CT imaging in over 4,000 patients attending rapid access chest pain clinics. This will define the most appropriate use of this emerging technology in the setting of diagnosing and treating patients with coronary heart disease and angina pectoris. This study will also lay the foundation for future studies to look at the potential prognostic value of this technology.

Current opinion suggests that the main utility of CT coronary angiography lies with the diagnosis and management of patients at intermediate risk of coronary heart disease [12,20] although recent evidence suggests that it may have a role in the care of patients with suspected acute coronary syndrome [31]. However, it could have a role even in apparently high-risk patients with stable symptoms, since CT may help identify patients with ‘false-positive’ stress tests that could potentially avoid invasive coronary angiography. Alternatively, it may allow early identification of patients at high risk of invasive coronary angiography (such as critical left main stem stenosis), those with anomalous coronary anatomy, or those for whom coronary revascularization is likely to be necessary. In the latter scenario, this will facilitate planning of invasive angiography and allow an interventional cardiologist to undertake follow-on percutaneous coronary intervention as required. This would potentially avoid the need for recurrent invasive angiography in situations where a noninterventional cardiologist performs the diagnostic angiogram.

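### CT accuracy is assessed only in patients who also have invasive angiography, and the CT result helps decide who has it, so uncorrected sensitivity would tend to be too high and specificity too low

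*Protocol article*

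**What the plan says.** Four statements in the protocol article bear on this point.

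- **Population.** Secondary endpoint (iv) is "the accuracy of CT coronary angiography compared with the gold-standard of invasive coronary angiography in those who receive both investigations" (Secondary endpoints).
- **Reference standard and target.** Diagnostic outcomes puts it this way: "accuracy of the CT coronary angiography will be determined by comparison with invasive coronary angiography (gold-standard) for the assessment of the number of vessels". The same section says that plaque burden cannot be compared between the two modalities.
- **Order and purpose.** CT takes place within 14 days of the clinic visit and "before invasive coronary angiography or other cardiac investigations" (Randomization). Doing CT ahead of any invasive angiogram is meant "to facilitate a decision to undertake or cancel this invasive investigation" (Investigation outcomes). The Discussion expects CT to pick out some patients with false-positive "stress tests that could potentially avoid invasive coronary angiography".
- **Other drivers of referral.** In general, high-risk patients, put at 10%, are expected to have invasive angiography. "Intermediate-risk patients (80%) will be treated and further investigated at the discretion of the clinician" (Clinic assessment).

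The two sets of angiograms are read independently and blind to each other (Image assessment). The article describes no reference standard for patients who do not have invasive angiography. It also places no limit on how the accuracy estimate is to be interpreted.

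**The concern.** The index test influences who receives the reference standard, and the accuracy endpoint then looks only at those who received it. If a positive CT makes invasive angiography more likely than a negative CT, CT-negative patients are under-represented among the verified. Both false negatives and true negatives are lost. Losing false negatives raises apparent sensitivity, and losing true negatives lowers apparent specificity.

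Blinded reading protects against one reading influencing the other. It does not change who is verified.

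What is at stake is the meaning of the reported accuracy. Figures from the doubly tested patients would partly describe referral behaviour and could be taken for CT performance in all scanned patients. The more effectively CT spares patients invasive angiography, which the article hopes for, the larger the distortion.

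**Working it through.** The plan gives no figure for this endpoint, so there is none to reproduce. The 2,069 per group was sized for the primary endpoint and enters here only as the size of the scanned arm.

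**Inputs**
- True sensitivity Se = 0.89 and specificity Sp = 0.96: the pooled 64-detector figures in the Background, used as illustrative true values.
- v+ and v−, the probabilities of invasive angiography after a positive and a negative CT: not in the article, so assumed and varied.

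**Step 1. Referral depends on the CT result alone**

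Apparent sensitivity = Se·v+ / [Se·v+ + (1−Se)·v−]

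Apparent specificity = Sp·v− / [Sp·v− + (1−Sp)·v+]

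| v+ / v− (assumed) | Apparent sensitivity | Apparent specificity |
|---|---|---|
| 50% / 20% | 0.445/(0.445+0.022) = 95.3% | 0.192/(0.192+0.020) = 90.6% |
| 70% / 10% | 0.623/(0.623+0.011) = 98.3% | 0.096/(0.096+0.028) = 77.4% |
| 80% / 5% | 0.712/(0.712+0.0055) = 99.2% | 0.048/(0.048+0.032) = 60.0% |

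Prevalence cancels from these formulas, but only because referral is taken to depend on CT alone.

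**Step 2. Clinical risk also drives referral**

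The article's risk split is 10% high, 80% intermediate and 10% low. Assumed prevalences are 60%, 20% and 5%. Assumed v+/v− are 80%/10% for intermediate and 60%/2% for low risk.

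- High risk verified at 95%/50%: apparent sensitivity 97.1%, specificity 77.3%.
- High risk all verified whatever CT shows: verified shares of the arm are true positives 0.1700, false negatives 0.0084, false positives 0.0244 and true negatives 0.1017. Sensitivity = 0.1700/0.1784 = 95.3%; specificity = 0.1017/0.1260 = 80.7%. The bias is smaller and runs in the same direction.
- CT has no influence within any risk group (100% of high, 30% of intermediate and no low-risk patients verified): 89.0% and 96.0%, so no bias.

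In the second of these settings the negative predictive value among verified patients is 0.1017/(0.1017+0.0084) = 92.4%. In the whole arm (prevalence 0.06+0.16+0.005 = 22.5%) it is 0.744/(0.744+0.02475) = 96.8%. Predictive values from verified patients therefore also need a label when clinical risk drives referral.

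**Step 3. Does a correction work?**

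Take 15% prevalence, which reproduces the 98% negative predictive value cited in the Background, and v+/v− of 80%/5%.

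- Proportion CT-positive = 0.89×0.15 + 0.04×0.85 = 0.1675.
- Predictive values in verified patients: positive 0.1335/0.1675 = 79.7%; negative 0.816/0.8325 = 98.0%.
- Begg-Greenes applies these to all scanned patients: sensitivity = 0.1335/(0.1335+0.0165) = 89.0%; specificity = 0.816/(0.816+0.034) = 96.0%.

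The true values are recovered. The precision is poor, however: verified CT-negative patients number 2,069×0.8325×0.05 ≈ 86, of whom about 2,069×0.0165×0.05 ≈ 2 would be false negatives.

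**The case against.** The strongest case on the other side has five parts.

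- **The subset is declared, and no measure is named.** The article openly limits the comparison to patients with both tests. It says accuracy for the number of vessels; sensitivity and specificity appear only where earlier literature is described. It nowhere says that the result will be applied to all scanned patients. This stands, and it is why the point is conditional on uncorrected figures being read as CT accuracy in the scanned arm.
- **Methods belong in the analysis plan.** A separate plan is announced and is not shown, and it may contain a correction. This stands for the choice of method. The restriction to doubly tested patients and the order of tests that creates the selection are, however, fixed in the article.
- **CT does not decide referral.** A reader might infer that the CT result alone determines who has invasive angiography. The article does not support that: CT is to help the decision, and clinical risk and clinician discretion also count. This reduces the size of the bias. It does not reverse it while a positive CT makes referral more likely.
- **Near-perfect sensitivity and poor specificity are not a forecast.** Only the more extreme assumed rates give such figures; at 50%/20% they are about 95% and 91%.
- **Vessel counting.** A reader might infer that counting diseased vessels will score disease in different vessels as agreement. The wording can equally be read as naming the feature that both modalities can show, in contrast to plaque burden. Both are reported on the 15-segment model, so vessel-matched comparison remains open. No error is shown here.

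**Conclusion.** The concern holds in a limited form. The article restricts the accuracy endpoint to doubly tested patients and gives CT a stated role in deciding who is doubly tested. Uncorrected sensitivity would then tend to be too high, and specificity too low, for the scanned arm. The direction rests on one condition, that a positive CT makes invasive angiography more likely than a negative one; the stated purpose of doing CT first points that way.

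The size is not established. Across the assumed rates in Step 1 it runs from about 95%/91% to 99%/60%, against illustrative true values of 89%/96%, and it shrinks if high-risk patients are referred regardless of CT. These figures also assume that sensitivity and specificity are the same in every risk group.

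The consequence is confined to one secondary endpoint. The primary comparison and its sample size do not use this estimate. A reader might also infer that policy would be misled, but the article ties policy use to the economic evaluation and does not say that this estimate feeds it.

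**What to change.** 1. Report predictive values or agreement among verified patients, and state that they apply to that subset.
2. Where sensitivity and specificity are reported for the scanned arm, add a verification-bias-corrected estimate. Either Begg-Greenes or inverse-probability weighting would do, using CT result, baseline risk category and baseline diagnosis, all of which the article plans to record.
3. Add a sensitivity analysis in which verification also depends on disease status beyond those variables.
4. Do not present the uncorrected values as CT accuracy in the clinic population.
5. Optionally, add a vessel-matched comparison from the 15-segment readings.

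This is analysis and reporting work on data already planned, with no change to conduct. The price is wider intervals, because few CT-negative patients may be verified, and a missing-at-random assumption for unverified patients that the data cannot confirm.
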